## Abstract

**Background:**

Most of the efforts to reduce teenagers' tobacco addiction have focused on smoking prevention and little on smoking cessation. A smoking cessation program (TABADO study), associating pharmacologic and cognitive-behavioural strategy, on a particularly vulnerable population (vocational trainees), was developed. This study aims to evaluate the efficacy of the program which was offered to all smokers in a population aged 15 to 20 years in Vocational Training Centers (VTC). This paper presents the TABADO study protocol.

**Methods:**

The study is quasi-experimental, prospective, evaluative and comparative and takes place during the 2 years of vocational training. The final population will be composed of 2000 trainees entering a VTC in Lorraine, France, during the 2008-2009 period. The intervention group (1000 trainees) benefited from the TABADO program while no specific intervention took place in the "control" group (1000 trainees) other than the treatment and education services usually available. Our primary outcome will be the tobacco abstinence rate at 12 months.

**Discussion:**

If the program proves effective, it will be a new tool in the action against smoking in populations that have been seldom targeted until now. In addition, the approach could be expanded to other young subjects from socially disadvantaged backgrounds in the context of a public health policy against smoking among adolescents.

**Trial registration:**

Clinical trial identification number is NTC00973570.

## Background

Tobacco is a major cause of preventable death in the world. According to the World Health Organization (WHO), smoking kills almost 5 million people each year. By 2030, this number is expected to double [1]. Every day, about 100,000 young people become addicted to tobacco in the world [2]. Preventing tobacco addiction is a public health priority designated by the Framework Convention for Tobacco Control of the WHO, in force since February 27, 2005. The adolescent population is a major target of this endeavour.

Almost all smokers become regular smokers before age of 20 [3]. In France, the average age of smoking initiation is 13.4 years, and 33% of teenagers at age 16 smoke every day [4]. Most of these young smokers are already dependent on tobacco [5]. In one study, 86% of teenage smokers said they were addicted; almost one-quarter of smokers aged 17-18 years said they had tried to stop but only a small proportion (5%) had managed to quit smoking [4]. Teenagers, even if they never smoked on a daily basis, may encounter significant difficulties in their attempts to quit. They experience the same withdrawal symptoms as do adults and underestimate the difficulty of quitting smoking [6].

Despite this, efforts to fight against smoking in the teenage population have focused largely on programs to prevent rather than quit smoking. Systematic surveys have identified twice as many trials aimed at preventing smoking [7] as trials aiming at smoking cessation [8,9]. To date, the effectiveness of different methods of quitting has been well demonstrated for adults [10], but evidence is lacking for adolescents. Two meta-analyses of trials of strategies for smoking cessation among teenagers have recently been published [8,9]. They stressed the advantage of programs based on a psychosocial approach and implemented within schools. They also demonstrated the moderate effectiveness of withdrawal programs among teenagers. In both studies, the authors concluded the need for further research because the data were still too fragmentary and were based on research studies of varying quality. In addition, evidence is lacking on the effectiveness of the combination of the two strategies for adolescents -- pharmacological and cognitive-behavioural -- which has demonstrated a synergistic effect on adults [10].

Moreover, programs for helping with smoking withdrawal offered to young people were developed on the basis of programs for adults and do not sufficiently take into account the specific forms of tobacco addiction among the young and their needs [10]. The traditional model for adults of the progressive development of nicotine addiction (from the experimental stage to the casual stage, then daily consumption increasing in frequency until the stage of addiction) [11], does not seem to fit young smokers. Some adolescents may have experienced their first symptoms of dependence before smoking daily or began smoking daily upon experiencing their first symptoms [6]. Their smoking habit is also more influenced by their environment (family, friends, and media) [12].

Many criteria for successful smoking cessation programs for teenagers have been described in the scientific literature [8,9,13,14]. The first lecture delivered in the programs should be informative but not preachy. Accessibility of treatment programs, notably by implementing them within schools (integrating the programs during school hours), and their cost-free character (for consultation and nicotine replacement substances) are important for attracting teenagers to become involved in smoking cessation programs. Few teenagers spontaneously consult a physician for withdrawal assistance because they tend to underestimate the difficulty of quitting. The anonymity of a program as regards parents is also crucial in increasing the motivation of young people to participate. Inclusion in a program must be voluntary. Finally, programs to aid in breaking the tobacco habit should be based more specifically on the psycho-social skills of the individual and should take into account the psychological aspects involved in the process of smoking withdrawal by means of individual and collective coaching. The combination of all these factors would allow for maximizing the participation rate of teenage smokers in a program to aid smoking withdrawal.

On this basis, a smoking cessation program (TABADO, TABagisme chez les ADOlescents) was developed by a team of tobacco addiction specialist physicians and public health researchers. This program combines pharmacological therapy with cognitive-behavioural therapy in a vocational school setting and is intended for adolescents from 15 to 20 years. It comprises 3 stages: (i) a lecture about general information on tobacco addiction for all students, both smokers and non smokers; (ii) an individual consultation with a tobacco addiction specialist for smokers; (iii) then 4 group sessions of follow-up and cognitive-behavioural therapy for smokers. The program is implemented within the institution during school hours. Consultations with tobacco addiction specialists and the group sessions are free, as are any substances that may be prescribed and dispensed as nicotine replacements.

The program was designed to be implemented within a particularly vulnerable population: vocational trainees. It was meant to enhance equity by reducing inequality in the access to health education programmes. Vocational trainees generally come from the least privileged socio-economic groups. Their health behaviour is often unfavourable, and their access to treatment is more difficult than for students of the same age who are enrolled in general school or university education [15].

However, before expanding such programs, their efficacy must be assessed. Therefore, we implemented this evaluation study among the vocational training centers (VTCs) of the Lorraine region, north-east France. The objective of this paper is to present the TABADO study protocol.

## Methods

This was a quasi-experimental, prospective, evaluative, comparative study. It compared 2 groups: the "intervention" group benefited from the TABADO program while the "control" group, drawn from the same training curriculum but from different VTCs, did not benefit from any specific intervention other than treatments and education that are usually available. The main objective of this study was to evaluate the efficacy a smoking withdrawal program offered as part of a comprehensive approach to prevention to all smokers in a population of young students in VTCs.

The primary outcome is the rate of smoking abstinence after 12 months, measured on the basis of the statements of the whole sample, not only among volunteers. The rate of abstinence is defined by the number of smokers who quit smoking at D_0_+12 months relative to the total number of smokers at D_0_, where D_0 _is the day of programme inception. Abstinence is defined here as quitting smoking for at least 1 month.

The secondary outcomes are three: (i) overall prevalence of tobacco usage in the study institutions at 12 months; (ii) students' motivation to quit smoking (motivational score) and frequency of attempts to quit within the 12 months after the intervention; (iii) and rate of withdrawal from the program among the volunteers after 12 months. This article deals only with the primary outcome of the study.

### Setting and participants

This observational study will cover all students entering a participating VTC in the Lorraine region (eastern France, 2.3 million inhabitants, 51 centers, 16,500 vocational trainees), during the school years 2007-2008 and 2008-2009. Students from vocational training courses with at least 2 years duration will be eligible. The control group will consist of students in the same kinds of courses, in different VTCs. Thus, the control group will have a psycho-socio-economic-cultural profile similar to that of the experimental group, without the control subjects being involved by the participants in smoking cessation, which might have occurred if the control subjects had belonged to the same VTC [16].

### Inclusion criteria

All students, males and females, registered in the VTC for at least a 2-year training period, and ranging 15 to 20 years old, will be included in the study. Criteria for non inclusion are subjects with current serious psychiatric disorders or who may be susceptible to decompensation upon quitting smoking (major depression), or smokers who are already involved in an ongoing attempt to quit, with medical monitoring.

### Sample size calculation

According to the literature, we can assume a maximum 5% spontaneous withdrawal rate [17]. We hope to double this rate among participants in the experimental group after 1 year. This 10% rate is based on the assumption of an effective participation of 50% of smokers in the experimental group, with a smoking cessation rate of 15% among them and the regular 5% for non-volunteers in the experimental group. With two groups of the same size, an α two-sided risk of 5% and a power of 85%, the number of smokers per group must be 500. Thus, the total number of students to be included is 2000 (anticipating that the prevalence of smoking is 50%).

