The group nature of the intervention and the risk of "behavioural contamination" require cluster sampling, rather than individual sampling. Given the small number of institutions and their great heterogeneity in terms of training programs, we preferred a reasoned attribution rather than randomization, which might not yield comparable groups and would not be effective in this case [16]. Our intervention is a community-based intervention (i.e. interventions in which the unit of allocation to receive preventive regimen is an entire community [25]. In other words, judgment criteria are measured over the entire population rather than among volunteers only. The main risk is a dilution of the effect in the case of low participation [26].

Finally, we chose the rate of continuous abstinence after 1 year to ensure optimal conditions for evaluation: the period of 1 year is usually accepted as a general long-term monitoring standard [27].

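### The 500 smokers per group contain no allowance for allocation by vocational training center, so the stated 85% power is an upper bound reached only if the intracluster correlation is essentially zero

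*Protocol article*

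**What the plan says.** All the inputs are in the protocol article under Sample size calculation. For the control rate, "we can assume a maximum 5% spontaneous withdrawal rate". For the intervention rate, "This 10% rate is based on the assumption of an effective participation of 50% of smokers in the experimental group", with 15% quitting among participants and 5% among the rest. With equal groups, a two-sided 5% level and "a power of 85%, the number of smokers per group must be 500", the total becomes 2000 trainees at an expected smoking prevalence of 50%. No ICC, design effect, number of VTCs or cluster size enters.

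The design is described elsewhere. Setting and participants draws the controls from other VTCs than the intervention group. The Discussion says that the group nature of the intervention and the risk of contamination "require cluster sampling, rather than individual sampling", treats the community as the unit of allocation, and explains why allocation was not random: "Given the small number of institutions and their great heterogeneity in terms of training programs".

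**The concern.** Trainees in one VTC share staff, peers, trades and local smoking norms, and in the intervention group they also share the delivery of the program. Their outcomes may be correlated, and a comparison between groups of VTCs then carries less information than the same number of unrelated smokers. The article recognizes clustering when it chooses the design, but sizes the study as if individuals had been sampled.

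What is at stake is how the result is read. If power is well below 85%, a non-significant difference says less about the program than the stated figure suggests. The article itself names dilution through low participation as the main risk, so there is little slack to absorb a further loss.

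**Working it through.** **1. Reproduce the stated figure.** Inputs from Sample size calculation: p₁ = 0.05; p₂ = 0.5 × 0.15 + 0.5 × 0.05 = 0.10; z = 1.960 (two-sided 5%) and 1.036 (85% power). Mean rate 0.075.

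n = [1.960·√(2 × 0.075 × 0.925) + 1.036·√(0.05 × 0.95 + 0.10 × 0.90)]² / 0.05² = [0.7301 + 0.3843]² / 0.0025 = 496.7, so 497 per group.

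Power at 500 = Φ[(0.05·√500 − 0.7301) / 0.3708] = Φ(1.046) = 85.2%.

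The formula for independent individuals thus uses up the 500. The room left for a design effect is 500/497 = 1.006. That no design effect was applied follows from this match, not only from the article's silence.

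**2. Assumptions for clustering.** The article gives neither the ICC nor the number of participating VTCs, so both are assumed here.

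- ICC: 0.001 to 0.02.
- VTCs per group, k: 6, 10 and 25, of equal size, with m = 500/k smokers each (83.3, 50 and 20).
- The value 6 is a rough guess from the regional figures. 16,500/51 is about 324 trainees per VTC, so about 162 entrants a year if every course lasts two years, and 1000/162 is about 6.
- The value 25 per group would take nearly all 51 centers in the region. It is a generous limit for what the article calls a small number.

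**3. Formulas.** Design effect DE = 1 + (m − 1) × ICC; effective n = 500/DE; power as in step 1 with effective n in place of 500. The VTC-based version uses a noncentral t with 2k − 2 degrees of freedom and noncentrality 0.05/√(0.1375/effective n), where 0.1375 = 0.05 × 0.95 + 0.10 × 0.90.

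Example, k = 6 and ICC 0.01: DE = 1 + 82.3 × 0.01 = 1.82; effective n = 274; power = Φ[(0.05·√274.2 − 0.7301)/0.3708] = Φ(0.264) = 60.4%. With 10 degrees of freedom it is 52.3%.

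**4. Results.** Power with 500 smokers per group, normal approximation (VTC-based t in parentheses):

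| VTCs per group | ICC 0.001 | ICC 0.005 | ICC 0.01 | ICC 0.02 |
|---|---|---|---|---|
| 6 | 82.4% (74.3%) | 71.5% (62.9%) | 60.4% (52.3%) | 45.4% (38.8%) |
| 10 | 83.5% (79.5%) | 76.8% (72.4%) | 69.2% (64.7%) | 56.9% (52.7%) |
| 25 | 84.6% (83.3%) | 81.9% (80.6%) | 78.7% (77.3%) | 72.5% (71.1%) |

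**5. Detectable rate.** Holding control at 5%, the intervention rate detectable with 85% power over the same ICC range (normal approximation) is 10.2% to 14.0% with 6 VTCs per group, 10.1% to 12.5% with 10, and 10.0% to 11.0% with 25. At 6 VTCs and ICC 0.01 it is 12.1%. Unequal VTC sizes would lower power further.

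**The case against.** **The arithmetic is right.** It is, for independent individuals: the 500, the 10% mixture and the 2000 all follow. The fault is the application to groups made of whole VTCs.

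**The unseen full protocol or analysis plan may handle clustering.** It may, and the absence of a VTC term from the regression outlined under Data analysis is no finding here. But a clustered analysis would not restore the power of a fixed 500 per group. The table presumes an analysis that respects clustering. Without one, the hazard would be false positives: at 6 VTCs and ICC 0.01 the type I error would be about 2·[1 − Φ(1.96/√1.82)] = 15%.

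**The 5% control rate is called a maximum.** This stands as a caution about size. With the article's mixture kept and a 3% background rate, the contrast is 3% against 9%, and power at effective n 274 is 84%. At 4% against 9.5% it is 73%. If the program instead doubles a lower rate, 3% to 6%, power at the same effective n falls to 40%. So this margin can work either way, and it was not put forward as an allowance for clustering.

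**Readings that go too far.** A reader might infer that the heterogeneity mentioned in the Discussion shows the design effect to be especially large here. The article speaks of heterogeneity in training programs, not in abstinence. Both groups come from the same kinds of courses, and training course is an adjustment variable, which may remove part of that variation. A reader might also infer that the entry years settle the number of clusters, because one place says "during the school years 2007-2008 and 2008-2009" and the abstract says "The final population will be composed of 2000 trainees entering a VTC in Lorraine, France, during the 2008-2009 period". The number of participating VTCs is a choice. The years would determine it only if 2000 were fixed and every VTC enrolled its full intake, which the article does not say.

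**Conclusion.** The point holds as a fault in the stated power. The 500 smokers per group allow for no clustering, while the article's own design allocates a small number of whole VTCs. At the stated 5% and 10%, the 85% is an upper bound that is reached only with an ICC of essentially zero. Even with 25 VTCs per group, an ICC of 0.005 brings power to 81.9%.

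The size of the shortfall cannot be fixed from the article. No single cell of the table, such as 60% or 45%, is a property of this trial. Each rests on an assumed ICC, an assumed number of equal-sized VTCs and the article's two rates. The firm conclusions are the direction of the error and that a small ICC matters more the fewer the VTCs.

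**What to change.** Keep the sample and rewrite the sample size paragraph:

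- State that 500 smokers per group gives 85% power only without clustering.
- Give the actual number of VTCs in each group.
- Report power for 5% against 10%, and the difference detectable at 85% power, over a stated ICC range such as 0.001 to 0.02, with degrees of freedom based on VTCs.

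The cost is one paragraph and a less favorable stated power. No trainees are added.

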### Intervention

The TABADO intervention takes place in 3 stages. First, a general information session on tobacco consumption is delivered to all teenagers, both smokers and non smokers. For the former wishing to join the program, this session is followed by individualized consultations with a team of tobacco addiction physicians who visit the VTC and deliver personal advice and assistance in choosing nicotine replacement therapy, if needed. Volunteers then benefit from a small group approach, supervised by the same physicians, consisting of discussion sessions to share experiences, strengthen motivation, and prevent relapse. There will be 4 sessions in total, comprising individual counselling and work in groups spread over 3 months (taking into account the availability of the trainees because of their alternate-week training schedule [1 week of school time with 3 weeks of work in the field]). In cases of a counter-indication to nicotine replacement treatment, only the cognitive-behavioral approach will be offered with a motivational interview and advice on strategies for resisting the desire to smoke.

### Data collection (figure 1)

**Figure 1 F1:**
[figure not shown]
**General diagram of the TABADO study**.

#### Monitoring data for all students

An initial assessment questionnaire on the smoking status of each trainee, socio-demographic data, knowledge, attitude, and behaviour will be completed by all students during the first visit, which will take place in the same period for both groups. A final questionnaire to evaluate smoking status will be completed at D_0_+12 months. It will contain the items included in the initial questionnaire and items allowing for assessment of changes in the perception of the health risks of smoking among trainees. The questionnaire will also include questions to measure changes over time in tobacco consumption among smokers. Thus, it will allow an overall assessment of the effectiveness of the intervention among the target population.

#### Monitoring data for smokers who volunteer for the program only

The in-depth assessment of tobacco consumption of volunteers will be based on a questionnaire used by the tobacco addiction specialist and on the case report form. Monitoring over time of the volunteer's tobacco consumption will be provided by 4 questionnaires completed by volunteers at each visit with the tobacco addiction specialist. At 6 months after the start of the intervention, volunteers will complete a follow-up questionnaire.

Ethical approval for the trial was requested from Inserm (*Institut National de la Santé et de la Recherche Médicale *- National Health and Medical Research Institute). The protocol was submitted to the national scientific and ethical bodies involved (CCTIRS and CNIL), who gave their approval. Written consent from the subjects participating in the program was collected by one of us (LM), after subjects were given information about the program and the study, as well as their right to refuse to take part in the program or to leave it at any time. Two types of data and consent forms were used: one aimed at volunteer aged less than 18 and their legal representatives (parents or guardian) and the other addressed to adult volunteers [>18 years].

### Data analysis

The experimental and control groups will be compared for abstinence rates reported at 12 months after the intervention by use of multivariate logistic regression adjusting for predefined characteristics (age, sex, and training course). The analysis will be "in intention to treat". All the smokers from the institutions will be taken into account, and subjects lost to follow-up will be considered non-abstaining smokers.

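### Whole training centers are allocated, but the stated primary model and the sample size treat smokers as independent, so any residual within-center correlation makes the interval too narrow and the type I error exceed 5%

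*Protocol article*

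**What the plan says.** **Allocation.** Under Setting and participants: "The control group will consist of students in the same kinds of courses, in different VTCs". Each VTC therefore belongs entirely to one group. The Discussion says that the group nature of the intervention and the risk of contamination "require cluster sampling, rather than individual sampling", and places the study among "interventions in which the unit of allocation to receive preventive regimen is an entire community". It adds that the institutions are few, that they differ widely in the courses they teach, and that they were assigned by judgement and not at random.

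**Primary analysis.** Under Data analysis, 12-month abstinence is compared "by use of multivariate logistic regression adjusting for predefined characteristics (age, sex, and training course". All smokers are kept, and those lost to follow-up count as not abstinent. The section mentions no VTC effect, random intercept, GEE, cluster-robust variance or cluster-level test.

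**Sample size.** The Sample size calculation section starts from "we can assume a maximum 5% spontaneous withdrawal rate" in controls and aims for 10% under intervention: "This 10% rate is based on the assumption of an effective participation of 50% of smokers in the experimental group". "With two groups of the same size", "an α two-sided risk of 5% and a power of 85" per cent, it arrives at 500 smokers per group. At 50% smoking prevalence that is 2000 students. The section gives no ICC, number of VTCs or design effect.

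**The concern.** The Discussion recognises that the unit of allocation is the institution, but the analysis and the sizing work at the level of the single smoker. Smokers in one VTC share staff, peers, school climate and, in the intervention group, the same group sessions and physicians, so their outcomes may be correlated. VTC is nested within group, so variation between VTCs feeds directly into the group comparison. A model without a VTC component leaves that variation out of the standard error.

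The primary result is at stake. With few institutions, chance differences between them could be reported as a programme effect with a small p-value, and the Conclusion envisages extending the programme to other disadvantaged young people if it proves effective.

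**Working it through.** **1. Reproduce the stated sample size.** Inputs from Sample size calculation: control rate 5%; intervention rate 0.5 × 15% + 0.5 × 5% = 10%; two-sided α 5%; power 85%; 1:1. Two-proportion formula with pooled variance and no continuity correction:

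n = [1.960·√(2 × 0.075 × 0.925) + 1.036·√(0.05 × 0.95 + 0.10 × 0.90)]² / 0.05² = 497 per group.

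Power at exactly 500 per group is 85.2%. The stated 500 is therefore the individual-level figure, with a design effect of 1.

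**2. Assumptions for the clustering.** Neither input is in the article.

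- *VTCs per group.* Setting and participants gives 51 centers and 16,500 trainees: 16,500/51 ≈ 324 per center, or about 162 entrants a year if courses last two years. Reaching 1000 students per group then takes about 6 VTCs from one year's entrants (1000/162 ≈ 6.2) and about 3 from two years' entrants (1000/324 ≈ 3.1). Both are shown because that section names two school years and the abstract names 2008–2009. Twenty-five per group is about the ceiling with 51 centers.
- *Residual ICC.* Assumed 0.005 to 0.02, after covariate adjustment.

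**3. Formulas.** With m = 500/(VTCs per group) smokers per VTC:

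- design effect DE = 1 + (m − 1) × ICC
- true SE / naive SE = √DE
- actual two-sided type I error of the nominal 5% test = 2 × [1 − Φ(1.96/√DE)]
- effective sample size = 500/DE

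Example with 6 VTCs per group, m = 83, ICC 0.01: DE = 1 + 82 × 0.01 = 1.82; √1.82 = 1.35; type I error = 2 × [1 − Φ(1.96/1.35)] ≈ 15%.

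**4. Type I error.** The rows for 6 and 3 VTCs are from a beta-binomial simulation (40,000 replicates, 5% abstinence in both groups, Wald test of the log odds ratio). The row for 25 is from the formula.

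| VTCs per group | ICC 0.005 | ICC 0.01 | ICC 0.02 |
|---|---|---|---|
| 25 (m = 20) | 6.1% | 7.2% | 9.5% |
| 6 (m = 83) | 9% | 14% | 22% |
| 3 (m = 167) | 13% | 21% | 33% |

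The formula gives about 10%, 15% and 23% for 6 VTCs per group, close to the simulation. At ICC 0 the simulated test stays at 4.6–4.8%, so the excess comes from the clustering. A t-test on VTC-level results held 4.6–5.0% in the settings with 6 and 3 VTCs per group. With 6 per group, the true SE is 1.19 to 1.63 times the naive one over this ICC range.

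**5. Power with a valid analysis at 500 smokers per group, ICC 0.01.**

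| VTCs per group | DE | Effective n | Power | Smokers per group for 85% (497 × DE) |
|---|---|---|---|---|
| 10 | 1.49 | 336 | 69% | 741 |
| 5 | 1.99 | 251 | 57% | 990 |

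These use the normal approximation. A t reference with few degrees of freedom lowers them further.

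**The case against.** **The article is a condensed account.** A short analysis section may leave the correlation structure to an analysis plan that is not shown, and a logistic model with a random VTC intercept would still be a logistic regression. This deserves weight, but the section does name the model and list its predefined adjustment set, and the sample size independently carries a design effect of 1. Sizing and analysis agree with each other, and both conflict with the Discussion. That is a stated choice and not merely an unreported detail.

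**Course adjustment.** A reader might infer that adjusting for training course does nothing about clustering, because courses occur in both groups. The article does not support that. Where VTCs differ in course mix, the adjustment removes that part of the between-VTC variance, and course mix is the only heterogeneity among institutions that the article names. It does not cover correlation from shared staff, peers or group sessions. This part of the objection stands: only the residual correlation matters, and it may be smaller than the crude one.

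**Size.** A reader might also take a particular inflated error rate as established. It is not. The article gives neither ICC nor VTC count, and the simulations are unadjusted, so they do not run the named model. At the mild end (25 VTCs per group, ICC 0.005) the error is about 6%.

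**Reach of the remedy.** Centers were assigned by judgement, so a cluster analysis corrects the precision but not systematic differences between the two sets of centers. This stands as well.

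**Conclusion.** The concern holds in conditional form. If the primary analysis is run as the Data analysis section describes it, any positive residual within-VTC correlation makes the interval too narrow and the type I error exceed 5%. The direction follows from the article's own allocation and model. The size depends on an assumed ICC and VTC count, and ranges from about 6% to 33% over the settings tabulated. The inflation vanishes only if the residual ICC is zero, which the article gives no reason to assume: it cites group delivery and contamination as grounds for clustering.

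The stated 85% power rests on the same independence and would not hold under a valid analysis if the residual ICC is positive.

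Two further inferences are not supported. One is that rewording the analysis section would be enough; that would leave the power claim uncorrected. The other is that the secondary outcomes share the fault: the article says that it covers only the primary outcome, and it states no analysis for the others.

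**What to change.** - Keep age, sex and training course, and make the primary analysis respect the VTC as the unit of allocation. Either use logistic regression with a random VTC intercept and a t reference with (number of VTCs − 2) degrees of freedom, or a two-stage analysis that compares covariate-adjusted VTC-level residuals by t-test. GEE is acceptable only with a small-sample correction, because with few VTCs the uncorrected sandwich variance is itself too small.
- State the number of VTCs per group and report the estimated ICC with the primary result.
- Restate the power at 500 smokers per group under an explicit ICC and VTC count, over a range if the ICC is uncertain. If 85% power is to be kept, show what that requires, such as the 741 or 990 smokers per group in the two examples above. More VTCs per group at the same total would also reduce the loss.
- Say plainly that the cluster analysis does not deal with confounding from the non-random allocation.

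**Cost.** The analysis needs no new data beyond each smoker's VTC. The interval can be expected to be wider and the stated power less favourable. Restoring 85% power would need more smokers or more VTCs; otherwise the lower power has to be acknowledged.
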